## Abstract

**Introduction::**

Peritoneal metastasis (PM) is a frequent condition in patients presenting with gastric cancer, especially in younger patients with advanced tumor stages. Computer tomography (CT) is the most common noninvasive modality for preoperative staging in gastric cancer. However, the challenges of limited CT soft tissue contrast result in poor CT depiction of small peritoneal tumors. The sensitivity for detecting PM remains low. About 16% of PM are undetected. Deep learning belongs to the category of artificial intelligence and has demonstrated amazing results in medical image analyses. So far, there has been no deep learning study based on CT images for the diagnosis of PM in gastric cancer.

**We proposed a hypothesis::**

CT images in the primary tumor region of gastric cancer had valuable information that could predict occult PM of gastric cancer, which could be extracted effectively through deep learning.

**Objective::**

To develop a deep learning model for accurate preoperative diagnosis of PM in gastric cancer.

**Method::**

All patients with gastric cancer were retrospectively enrolled. All patients were initially diagnosed as PM negative by CT and later confirmed as positive through surgery or laparoscopy. The dataset was randomly split into training cohort (70% of all patients) and testing cohort (30% of all patients). To develop deep convolutional neural network (DCNN) models with high generalizability, 5-fold cross-validation and model ensemble were utilized. The area under the receiver operating characteristic curve, sensitivity and specificity were used to evaluate DCNN models on the testing cohort.

**Discussion::**

This study will help us know whether deep learning can improve the performance of CT in diagnosing PM in gastric cancer.

## Introduction

1

Although it is steadily declining in incidence, gastric cancer (GC) remains one of the most common and deadly tumor in the world. According to GLOBOCAN 2018 data, GC is the 5th most common and the 3rd most deadly cancer.^[1]^ Peritoneal metastasis (PM) is a frequent condition in patients presenting with GC, especially in younger patients with advanced tumor stages.^[2]^ Given the detrimental influence of PC on survival, efforts should be undertaken to further explore the promising results that were obtained in preventing or treating this condition with multimodality strategies.^[2]^ Therefore, detecting noninvasively PM of GC before surgery would be crucial for avoiding unnecessary resection and selecting optimal therapy in clinical practice.^[3–8]^

CT is the most common noninvasive modality for preoperative staging in GC.^[4,6,8–10]^ Omentum cake, large amounts of ascites, and parietal peritoneal thickening are typical CT features of PM.^[11]^ However, the challenges of limited CT soft tissue contrast result in poor CT depiction of small peritoneal tumors, which are often indistinguishable from adjacent bowel, mesentery, and mucin.^[12–14]^ These features were not present in all patients with PM, the sensitivity for detecting PM remains low.^[11,15–17]^ About 16% of PM are undetected.^[18]^ PM-negative of patients with GC diagnosed by preoperative CT were confirmed with PM during subsequent surgeries or laparoscopies, which is known as occult PM.^[11,19]^ At present, laparoscopy is the most reliable preoperative method to identify clinically occult PM in patients with GC.^[4,7–9,12,20]^ However, laparoscopy is an invasive and costly procedure and is not systematic in clinical practice. Therefore, we should develop better noninvasive methods to diagnose PM beyond conventional imaging.

There are 2 kinds of medical image analysis method that have entered the stage of rapid development: radiomics and deep learning.^[21]^ Recently, several studies have shown that radiomics based on CT can help diagnose PM in GC.^[22–24]^ Deep learning belongs to the category of artificial intelligence and has demonstrated amazing results in medical image analyses, such as detecting diabetic retinopathy in fundus photographs,^[25]^ classifying skin cancer from skin photographs,^[26]^ and detecting metastasis on pathologic images,^[27]^ and so on. So far, there has been no deep learning study based on CT images for the diagnosis of PM in GC.

We proposed a hypothesis: CT images in the primary tumor region of GC had valuable information that could predict occult PM of GC, which could be extracted effectively through deep learning.

## Participants and methods

2

### Study aims

2.1

The aim of this study is to develop a deep learning model for accurate preoperative diagnosis of PM in GC.

### Study design/setting

2.2

This is a single-center, retrospective, cross-sectional clinical study. The CT data from the Surgical Gastric Cancer Patient Registry of West China Hospital (id: WCH-SGCPR-2019-08), all of which were anonymous.

### Study registration

2.3

This clinical trial has been registered on the Chinese Clinical Trial Registry (www.chictr.org.cn), and the registration number is ChiCTR1900028437.

### Eligibility criteria (Fig. 1)

2.4

The patients with GC underwent surgery or laparoscopic exploration at our hospital from January 2013 to December 2016 were retrospectively collected.

**Figure 1 F1:**
[figure not shown]
Flowchart of the patient selection and patient exclusion.

#### Exclusion criteria

2.4.2

(1)Previous abdominal surgery.(2)Previous abdominal malignancies or inflammatory diseases.(3)Time intervals between CT and laparoscopy or operation longer than 2 weeks.(4)Poor CT image quality for post-processing due to artifacts.

### Intervention

2.5

This study is a retrospective analysis of CT images and deep learning modeling, with no intervention measures for patients.

### Deep learning methods

2.6

#### CT image acquisition and preprocessing

2.6.1

All patients underwent enhanced CT examination within 2 weeks before surgery or laparoscopic exploration.

Portal vein phase CT images were exported to the ITK-SNAP software (version 2.2.0; www.itksnap.org) for manual segmentation. The lesions of GCs were manually recognized by a radiologist with 5 years’ experience in gastroenterology imaging) and confirmed by another abdominal radiologist with 14 years’ experience in gastroenterology imaging). Two radiologists reviewed all slices of a patient and selected 1 slice with the largest tumor area and manually drawn along the margin of the lesion. The gastric lumen and artifacts were carefully avoided. The images with ROIs derived from ITK-SNAP as input were used to construct the deep learning-based model.

#### Data management

2.6.2

For the development of the deep learning-based model, all patients’ CT images with PM-negative and patients’ CT images with occult PM, were randomly allocated into 1f of 2 cohorts:

(1)the training data cohort contains 70% patients of occult PM and 70% patients of PM-negative, and 5-fold cross-validation was used to optimize the network weight;(2)the in-house validation data cohort comprising 30% patients of occult PM and 30% patients of PM-negative to evaluate the predictive performance of the deep learning-based model.

#### Development of the deep learning-based model

2.6.3

In brief, we adopted a deep convolutional neural network with Depthwise Convolution blocks and Fully Connection layer constructing a classifier. This classifier was designed to determine the probability of a patient having an occult PM. For training the model can predict occult PM, we used weighted cross-entropy loss to supervise the model's parameter optimization direction.

Finally, for each input of CT image, the deep learning-based model provided a continuous value between 0 and 1 as the probability of occult PM, and the process is shown in Figure 2.

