#### Evaluation of the deep learning-based model

2.6.4

We get 5 different single models via 5-fold cross-validation. Then, we carry out all 5 models as a vanilla ensemble model, averaging the predicted risk values of the 5 single models. We analyzed the ROC consistency between the Vanilla ensemble model and each single model. Moreover, we selected each single model as the candidate model based on the above analysis results, and then assembled these to obtain our ensemble model. We evaluate the performance of models on the in-house validation cohort.

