### Statistical analysis

2.10

The differences of continuous variables were analyzed by the Mann–Whitney *U* test, and the differences of categorical variables were analyzed by the Chi-square test. The accuracy of the deep learning-based model was assessed with the receiver operating characteristic (ROC) curve and area under the ROC curve. Delong test was used to compare the ROC curves of models. The calibration of the model was assessed using the calibration curves. In addition, sensitivity and specificity for classification were evaluated.

For the deep learning-based model, 2 different probability values were selected as classification thresholds based on the results of the in-house validation cohort: a high sensitivity threshold (75% sensitivity on in-house validation) and a high specificity threshold (75% specificity on in-house validation). Considering the group imbalance in the in-house validation cohort, we used bootstrap (resampled the in-house validation cohort 1000 times) and calculated the 95% confidence interval. Finally, the decision curve was conducted to evaluate our approach usefulness by quantifying the net benefits at different thresholds probabilities.

All these statistical analyses were performed with SPSS 22.0. A 2-tailed *P*-value less than .05 was considered statistically significant.

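### A class-weighted training loss feeds an uncorrected output, labelled as a probability, into the calibration and decision curves

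*Protocol article*

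**What the plan says.** All references are to the protocol article.

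- **Section 2.6.3 (model development), loss:** "we used weighted cross-entropy loss to supervise" the fitting of the network's parameters. The weights are not given.
- **Section 2.6.3, output:** for each image the model "provided a continuous value between 0 and 1 as the probability of occult PM".
- **Section 2.6.4 (model evaluation):** the first ensemble is formed by "averaging the predicted risk values of the 5 single models". A second ensemble is then assembled from selected single models. No rescaling is mentioned for either.
- **Section 2.10 (statistical analysis), calibration:** "The calibration of the model was assessed using the calibration curves".
- **Section 2.10, clinical usefulness:** "the decision curve was conducted to evaluate our approach usefulness by quantifying the net benefits at different thresholds probabilities".
- **Section 2.10, class mix:** the bootstrap is introduced with "Considering the group imbalance in the in-house validation cohort". The ratio is not given.
- **Section 2.6.2 (data management):** the 70/30 split is made within each class, so the validation cohort keeps the class mix of the full dataset.

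**The concern.** Calibration curves and net benefit both need absolute risks. A calibration curve compares the predicted with the observed proportion. Net benefit at threshold t flags patients whose predicted risk is at least t and charges each false positive the odds t/(1-t), so the cut-off and the penalty must refer to the same risk scale.

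A class-weighted loss breaks that link. It teaches the network the risk in a reweighted population, not in the patients seen. Because the split preserves the class mix, nothing in the validation cohort undoes the weighting.

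The Discussion offers the model as a way to choose candidates for laparoscopic exploration, and the decision curve is the planned analysis that speaks to that use. If it is computed on inflated risks, it judges the model at cut-offs other than those on its axis, and part of what it shows is the choice of loss.

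**Working it through.** **Plan's own figure.** The article gives no weight, prevalence, expected AUC or net benefit, so there is nothing to reproduce on this point. Its one computed figure, a minimum of 109 patients (section 2.9), comes without inputs and does not enter the argument.

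**Step 1: effect of the weight.** Let p be the true risk and w the weight on PM cases relative to PM-negative cases. The expected loss is -[w p ln q + (1-p) ln(1-q)]. Setting its derivative in q to zero gives

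q = w p / (w p + 1 - p), so odds(q) = w × odds(p).

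The shift is ln(w) on the logit scale. A check with weighted logistic regression (200,000 training records) moved the intercept by 1.658 against ln(5.25) = 1.658, and by 0.694 against ln(2) = 0.693.

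**Step 2: what the output then means.** With w = 5.25, a true risk of 0.05 is output as 0.22, 0.16 as 0.50 and 0.30 as 0.69. Conversely, a nominal threshold t acts at true risk t/(t + w(1-t)). For t = 0.20 this is 0.20/(0.20 + 5.25 × 0.80) = 0.045.

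**Step 3: net benefit.** Assumptions, none of them from the article:
- Prevalence π of 10%, 16% or 30%.
- w equal to the balancing weight (1-π)/π, or a milder w = 2.
- An equal-variance binormal score with AUC 0.75, so the class means differ by √2 × Φ⁻¹(0.75) = 0.954.

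Net benefit = π × sensitivity - (1-π) × (1 - specificity) × t/(1-t).

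At t = 0.20, π = 0.16, w = 5.25:
- Weighted output: 0.16 × 0.973 - 0.84 × 0.836 × 0.25 = 0.156 - 0.175 = -0.020 (unrounded inputs). 86% of patients are flagged.
- Corrected output: 0.16 × 0.576 - 0.84 × 0.223 × 0.25 = 0.092 - 0.047 = 0.045. 28% are flagged.

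The same calculation over the range, at t = 0.20:

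| Prevalence | w | Mean output | Net benefit, weighted | Net benefit, corrected | Treat all |
|---|---|---|---|---|---|
| 16% | 5.25 | 0.436 | -0.020 | 0.045 | -0.050 |
| 16% | 2 | 0.257 | 0.029 | 0.045 | -0.050 |
| 10% | 9 | 0.425 | -0.091 | 0.015 | -0.125 |
| 30% | 2.33 | 0.462 | 0.146 | 0.162 | 0.125 |

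Treat none is 0. The corrected mean output equals the prevalence in every row.

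**Step 4: what does not move.** The map from p to q is monotone, so a model's ranking is preserved. AUC, the DeLong comparison, and the operating points set at 75% sensitivity and 75% specificity are unchanged. In the logistic check at 16% prevalence, AUC was 0.780 with and without weighting.

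**The case against.** Several counter-arguments have force.

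- **The calibration curve is not made wrong.** A reader might infer that weighting invalidates it. It does not: the curve would show the over-prediction faithfully, and so the plan already contains the diagnostic. What stands is that the plan names no action to follow, and that the curve would mainly report the loss function.
- **The decision curve correctly evaluates the rule of acting when the raw output reaches t.** This is true, but the article calls that output a probability, so its threshold axis will be read as true risk. On that reading, net benefit is understated relative to what the same ranking can deliver.
- **The reversal to harm depends on assumptions.** A reader might infer that the plan will show a useful model to be harmful. This happens in two of the four scenarios; in the other two the model still beats both default strategies. Nor is 16% a documented prevalence: in the Introduction it is the share of PM that goes undetected. Here it is only one value in a range.
- **An exact shift of ln(w) is not assured.** The stated minimum of 109 patients gives about 0.70 × 109 = 76 for training, and about 0.80 × 76 = 61 per fold model. A network that overfits so few patients, and is then averaged, will be miscalibrated in other ways too. This limits confidence in the size.
- **The article is condensed.** A fuller protocol might contain a recalibration step. That limits certainty, but the article does state the loss, the probability label and both downstream uses.

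**Conclusion.** The point holds, conditionally. As written, an output trained under a weighted loss is labelled a probability and used in two analyses that need absolute risks, with no correction named. This assumes that the weighting is by class and favours PM cases, which the acknowledged imbalance makes likely but the article does not say. The distortion vanishes only if the relative weight is 1.

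Under that reading the direction is stable: predicted risk is too high and net benefit too low. The size is not known. Across the assumed scenarios the loss in net benefit at threshold 0.20 runs from 0.016 (0.162 - 0.146, or 0.045 - 0.029) to 0.106 (0.015 + 0.091), for AUC 0.75 and a model at its weighted optimum.

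The documents do not support a claim that the study's discrimination results are affected. AUC, sensitivity and specificity, the measures named in the abstract, rest on ranking. Only the calibration and decision-curve results are exposed, so this is a should-fix point, not a critical one.

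**What to change.** State the class weights in section 2.6.3. In section 2.10, add one step before the calibration and decision-curve analyses: fit a logistic recalibration (intercept and slope) on out-of-fold predictions from the training cohort, lock it, and apply it to the final ensemble score in the validation cohort. Report both analyses on the recalibrated risk.

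A simpler, approximate alternative is to divide each single model's output odds by w before averaging, that is p = q/(q + w(1-q)). This removes the weight but not any miscalibration from overfitting.

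The cost is one analysis step and a sentence or two of text, with no new data. The downside is some imprecision in the recalibration map, because the training cohort is small and the out-of-fold scores come from single models, whose spread differs from that of the averaged ensemble.

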**Figure 2 F2:**

Deep learning workflow in this study.

#### Evaluation of the deep learning-based model

2.6.4

We get 5 different single models via 5-fold cross-validation. Then, we carry out all 5 models as a vanilla ensemble model, averaging the predicted risk values of the 5 single models. We analyzed the ROC consistency between the Vanilla ensemble model and each single model. Moreover, we selected each single model as the candidate model based on the above analysis results, and then assembled these to obtain our ensemble model. We evaluate the performance of models on the in-house validation cohort.

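### The plan does not fix which data or rule select the members of the final ensemble; if the in-house validation cohort was used, the AUC reported on it is optimistic

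*Protocol article*

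**What the plan says.** Section 2.6.2 (Data management) splits the patients into two cohorts. The first is a training cohort with 70% of each outcome group, in which "5-fold cross-validation was used to optimize the network weight". The second is "the in-house validation data cohort comprising 30% patients of occult PM and 30% patients of PM-negative to evaluate the predictive performance" of the model. The abstract calls this second cohort the testing cohort. No third set is described.

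Section 2.6.4 (Evaluation of the deep learning-based model) then gives this sequence:

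1. "We get 5 different single models via 5-fold cross-validation".
2. A vanilla ensemble is formed by "averaging the predicted risk values of the 5 single models".
3. "We analyzed the ROC consistency between the Vanilla ensemble model and each single model". No cohort is named.
4. "we selected each single model as the candidate model based on the above analysis results, and then assembled these to obtain our ensemble model". No rule is given.
5. "We evaluate the performance of models on the in-house validation cohort".

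Section 2.10 (Statistical analysis) adds that "Delong test was used to compare the ROC curves of models", without saying which models or which cohort.

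**The concern.** The model to be reported is the product of a data-driven selection step for which no data are reserved. A test cohort gives an unbiased AUC only for a model that was fixed without it. If the ROC comparison in step 3 was run on the in-house validation cohort, the members were chosen partly for the chance features of those patients, and the same patients then supply the AUC. Any DeLong comparison of the final ensemble with the single models on that cohort would lean the same way.

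The criterion is also partly circular, because each single model contributes one fifth of the average it is compared with.

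AUC is the leading accuracy measure in both the abstract and section 2.10, so this step bears on the main result.

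**Working it through.** **Step 1. The plan's own figure.** The only numerical design figure is the minimum sample size of 109 (section 2.9). The article gives no formula or precision target, so 109 cannot be reproduced. This point does not depend on it. It serves only to set the smallest test cohort: 0.30 × 109 = 32.7, about 33 patients.

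**Step 2. Where can the comparison be made out of sample?** In 5-fold cross-validation each training patient is held out from one model and used to fit the other four. On any held-out fold, one single model is out of sample, but four of the five components of the average are in sample. The average therefore has no out-of-sample ROC curve anywhere in the training cohort. Of the data described, only the 30% cohort allows an out-of-sample comparison of the average with all five members.

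**Step 3. The possible readings.**

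| Data and action in steps 3 and 4 of section 2.6.4 | Effect on the AUC in the 30% cohort | Quality of the step |
|---|---|---|
| Members selected on the in-house validation cohort | Optimistic | Test cohort no longer independent |
| Members selected on training-cohort ROC curves | No bias from this step | Selection rests on overfitted curves |
| All five kept, same averaging | No bias from this step | Redundant: it is the vanilla ensemble again |

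**Step 4. Size under the first reading.** Assumptions, none of them fixed by the article:
- Total N is 109, 300 or 500, which gives test cohorts of 33, 90 or 150.
- Prevalence is 16% or 30%. The 16% is borrowed from the Introduction, where it is the share of peritoneal metastases that go undetected, not the prevalence in this cohort.
- The five models are exchangeable with normally distributed scores. The correlation ρ between models is 0.5 or 0.8. The mean shift δ is 0 (no signal) or 0.8.
- There are 1,000 simulated test cohorts per setting.

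The true AUC of a mean of k models is Φ(δ / √(2(ρ + (1 − ρ)/k))). With δ = 0.8 and ρ = 0.5:
- k = 5: Φ(0.8/√1.2) = 0.767
- k = 3: Φ(0.8/√1.333) = 0.756

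With ρ = 0.8 the values are 0.731 and 0.728.

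Optimism is the mean apparent AUC minus the true AUC:

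| Rule applied on the test cohort | With signal | No signal |
|---|---|---|
| All five averaged, no selection | about 0 | about 0 |
| Three models closest in AUC to the average | 0.01 to 0.03 | about 0 |
| Three models with the highest AUC | 0.01 to 0.05 | 0.01 to 0.07 |
| Best of all 31 subsets | 0.01 to 0.07 | 0.03 to 0.13 |

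Two worked entries at N = 109, prevalence 16%, ρ = 0.5, δ = 0.8 (5 positives among 33):
- Closest three: 0.784 − 0.756 = 0.028.
- Highest three: 0.804 − 0.756 = 0.048.

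The best-subset row is measured against the true five-model AUC: 0.836 − 0.767 = 0.069 in the same setting, and 0.633 − 0.500 = 0.133 without signal.

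The closest-three rule is optimistic only when there is signal. An average then has a higher AUC than its members, so the members closest to it tend to be those that did best by chance.

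**Step 5. A milder consistency rule.** Suppose every model that a DeLong test does not separate from the average is kept (2,000 cohorts per setting; 5/28 or 20/100 patients with and without metastasis; ρ 0.5 or 0.85). Net of simulation error, optimism is 0.002 to 0.018 at a single-model AUC of 0.70 and about 0 at 0.50. All five models are kept in 26% to 83% of runs at an AUC of 0.70.

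**The case against.** A reader might infer that the final model was tuned on its own test data and that its AUC is therefore biased. The article does not say so. Section 2.6.4 names no cohort for the ROC comparison. Its order (build, compare, select, assemble, then evaluate on the in-house validation cohort) fits an ensemble completed before that cohort was opened, and section 2.6.2 gives the cohort an evaluating role. That an out-of-sample comparison was possible only there does not show that one was made there. The selection sentence can also be read as keeping all five models. This stands, and the bias can be asserted only conditionally.

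A reader might also take the largest simulated figures, up to 0.13, as the likely size. They come from searching for the highest AUC, whereas the article speaks of consistency, for which the excess is about 0 to 0.03. No significance rule is stated either, so the DeLong-based rule above is one possibility and not the plan's. This also stands.

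Finally, this is a condensed article and its workflow figure is not available, so cohort and rule may be stated elsewhere. That stands in part. A missing detail alone would not be a finding, but the two-cohort design and the stated sequence are in the article itself, and none of the three readings gives the step a sound purpose. Two features make the first reading plausible without proving it. The comparison sits under Evaluation, where the in-house validation cohort is the only cohort named, and section 2.10 openly chooses both classification thresholds on that cohort. The threshold choice is a separate matter and does not itself affect the AUC.

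**Conclusion.** The point holds in conditional form. The article does not fix the data or the rule by which the vanilla ensemble becomes the final one. If the in-house validation cohort was used, the final ensemble's AUC on it, and any DeLong comparison with the single models, is optimistic: by roughly 0 to 0.03 for a consistency-type rule, and by more if members were picked for the highest AUC. These sizes rest on assumed cohort sizes, prevalence, between-model correlation and exchangeable models. If training-cohort curves were used, the test AUC is not biased by this step, but the choice rests on overfitted curves. If all five were kept, the step does nothing. A definite statement that the AUC is biased is not supported. What is supported is that the step has no good justification under any reading and is easily removed.

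**What to change.** State that the mean of all five fold models is the single final model, fixed before the in-house validation cohort is scored, and evaluate it there once. Drop the further assembly step.

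If members must be selected, give the rule in advance and apply it only to each model's own held-out fold within the training cohort. Such a rule would be noisy at the minimum sample size: 0.70 × 109 / 5 is about 15 patients per fold, and at an assumed 16% prevalence only about 2 of them would be positive. That favours not selecting at all.

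If the selection has already been made, name the cohort and the rule used, and report the five-model average as the primary result.

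The cost is a change of wording and less analysis work. The reported AUC may be slightly lower.
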